### Design and Treatment

The study is a randomized, double-blind, placebo-controlled, parallel groups clinical trial with participants randomized to receive Ubiquinol (200 mg/day) or placebo over a 90-day period (Ubiquinol is the reduced form of CoQ_10_). All eligible participants will be assigned to treatment group A or B using a computer-generated random number generator by a disinterested third party. Ubiquinol and placebo will be matched in appearance. Randomization codes will be kept in a password protected computer file and only opened in case of emergency.

### Participants

A total of 128 healthy elderly participants (52 per group) aged 60+ years will be randomized. The sample size was selected on the basis of power analysis with G*Power 3.1.9.2, which revealed that with two treatment groups and two primary time points and specifying a significance level of *p* < 0.05, there is an 80% chance of detecting a small-medium effect size (cohen’s *f* = 0.14) for the time × treatment group interaction. Inclusion criteria will include being male or female aged 60 years or older, fluent in written and spoken English, normal or corrected-to-normal eyesight and good general health on the basis of medical history. Exclusion criteria will include being a current smoker, or having a history of the following medical conditions: diabetes, epilepsy, PD, dementia, stroke (or other neurological conditions), traumatic brain injury, current anxiety, depression, alcohol or substance dependence, endocrine, gastrointestinal or bleeding disorder, and uncontrolled hypertension (as determined by a systolic blood pressure >160 mm Hg or diastolic blood pressure >90 mm Hg). Participants will also be excluded if they are currently using over-the-counter herbal or nutritional supplements with known effects on cognition and mood, anti-coagulant drugs, anti-depressants (e.g., selective-serotonin reuptake inhibitors) or anxiolytics (e.g., benzodiazepines).

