### Statistical Analysis

The primary analysis will involve an intention-to-treat (ITT) examination of the effects of treatment (CoQ_10_ Ubiquinol vs. placebo) on CogTrack index scores (attentional intensity index, sustained attention index, working memory capacity index, episodic memory capacity index, and speed of retrieval index) at 90-days compared to baseline. Repeated measures analysis of variance (ANOVA) will be used to examine treatment and study visit × treatment interaction effects, using a subject-specific random intercept term, treatment group as a between-group factor (CoQ_10_, placebo) and study visit as a repeated within-group factor (baseline, 90-days). Pearson’s *r* correlations will be used to explore the relationships between demographic variables (i.e., age, weight, height, education, gender) and CogTrack composite scores, and in the case of significant associations (*p* < 0.05), demographic variables will be included as covariates in the analysis.

Similar statistical techniques will be used to investigate the effects of treatment on secondary outcomes, as well as the CogTrack composite scores at 30- and 60-day time points. Results will be presented as effect sizes using 95% confidence intervals. Overall compliance to treatment will be analyzed by counting each participants remaining supplements at the completion of the trial.

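### The randomised total (128) and the per-group number (52) cannot both be right in a two-arm trial, and they cannot both match the stated 80% power

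*Protocol article*

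**What the plan says.** The Participants section gives the target in one sentence: "A total of 128 healthy elderly participants (52 per group) aged 60+ years will be randomized". It then gives the basis: "The sample size was selected on the basis of power analysis with G*Power 3.1.9.2". The inputs listed are "with two treatment groups and two primary time points" and "specifying a significance level of *p* < 0.05". The result claimed is that "there is an 80% chance of detecting a small-medium effect size", namely a Cohen's f of "0.14) for the time × treatment group interaction".

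Two other sections fix the setting. Design and Treatment describes a parallel-group trial with "participants randomized to receive Ubiquinol (200 mg/day) or placebo over a 90-day period", so there are two arms. Statistical Analysis specifies a repeated measures ANOVA with "study visit as a repeated within-group factor (baseline, 90-days" as its two levels, which agrees with the two time points in the power calculation.

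The article mentions no third arm, no unequal allocation, no attrition rate and no correlation between the baseline and Day-90 scores.

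**The concern.** The total and the per-group number hang on the same verb in the same sentence: both are said to be randomised. In a two-arm trial they contradict each other. This is a wrong statement in the text shown, which is different from a detail that a condensed article may leave to a fuller document.

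Two things are at stake. The first is the recruitment target. A reader cannot tell whether the trial is complete at 104 or at 128, so nobody can later judge whether it met its target or stopped early. The second is the power claim. The article ties 80% power at f = 0.14 to the sample size, but that claim cannot be true of both sizes, and the article does not say which one it belongs to.

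**Working it through.** **Step 1. Arithmetic, with no assumption.** 2 × 52 = 104. 128 / 2 = 64. Difference: 128 − 104 = 24 in total, 12 per arm.

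**Step 2. Reproduce the stated power.**

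Inputs from the Participants section: k = 2 groups, m = 2 time points, f = 0.14, alpha = 0.05, power 80%, G*Power, time-by-treatment interaction.

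Input not in the document: the within-person correlation rho. I assume 0.5, the usual G*Power default, and vary it in step 3.

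Formula for the within-between interaction with sphericity (automatic for two time points): power is the upper tail of a noncentral F beyond the 5% critical value, with

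- lambda = f² × N × m / (1 − rho)
- df = (k − 1)(m − 1) = 1 and (N − k)(m − 1) = N − 2

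At rho = 0.5, lambda = 0.0196 × N × 2 / 0.5 = 0.0784 × N.

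| N | per group | lambda | power |
|---|---|---|---|
| 102 | 51 | 8.00 | 79.97% |
| 104 | 52 | 8.15 | 80.7% |
| 128 | 64 | 10.04 | 88.2% |

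So 104 is the smallest equal-group total that reaches 80%, and it coincides with the printed 52 per group. At N = 128 the effect detectable with 80% power is f = 0.125 (lambda = 0.015625 × 128 × 4 = 8.0, power 80.1%).

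Cross-check on the change score: the between-group difference in change is 4f = 0.56 standard deviations. The SD of change is √(2(1 − rho)) = 1 at rho = 0.5. The normal approximation needs 51 per group and gives 81.5% power at 52 per group and 88.6% at 64 per group.

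**Step 3. Vary the unstated correlation.**

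| rho | N needed for 80% | power at 104 | power at 128 |
|---|---|---|---|
| 0.3 | 144 | 66.7% | 75.7% |
| 0.37 | 130 | 71.2% | 79.97% |
| 0.4 | 124 | 73.3% | 81.9% |
| 0.5 | 104 | 80.7% | 88.2% |
| 0.6 | 84 | 88.5% | 94.0% |

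The correlation at which 128 gives exactly 80% is 0.3705, so the row for 0.37 falls just short. The correlation at which 104 gives exactly 80% is 0.490. Power rises with N at any fixed correlation, so no single value gives 80% at both sizes.

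**Step 4. Other settings, at rho = 0.5 where it applies.** A 10% level needs 82 participants, and four time points instead of two need 72. The alternative effect-size conventions in G*Power give 29% to 35% power at these sizes. A 1% level (0.05 / 5 index scores) gives 59% at 104 and 71% at 128. None of these makes 128 the 80% figure.

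**Step 5. Could dropout link the two numbers?** 1 − 104/128 = 0.1875, and 102 / (1 − 0.20) = 127.5, which rounds up to 128. Either would work arithmetically. Both rates are back-calculated from the conflicting figures; neither is in the article.

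**The case against.** The strongest reply is that 128 is simply the recruitment target and 104 the number needed at the end, with the dropout allowance set out in a fuller protocol that is not shown. On that reading the design is sound, and at a correlation of 0.5 power stays at or above 80% even after 24 losses. This is plausible, and the absence of an attrition rate from a journal article is not an error in itself. It does not rescue the sentence, though, which gives 52 per group as a number randomised. A slip of 52 for 64 would also explain the text, and the reader cannot tell the two apart.

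A reader might be tempted by three stronger conclusions that the document does not support.

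- *That only 104 reproduces the 80%.* This depends on the correlation of 0.5, which is my assumption. The exact match makes 104 the likelier calculated size but does not prove it, since a correlation near 0.37 would make 128 the match.
- *That 52 per group is the analysable number.* The article never calls it evaluable or completing.
- *That the trial is underpowered.* Loss of power follows only if recruitment stops at 104, which the text does not say. Even then it is gradual: at a correlation of 0.5, losing 2 of 104 gives 79.97% and losing 10 gives 76.6%.

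**Conclusion.** The contradiction is certain and rests on no assumption: in this two-arm trial, 128 randomised is not 52 per group. The recruitment target is ambiguous by 24 participants.

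What follows for power is conditional on the unstated correlation. At 0.5, the 80% claim belongs to 104 and understates power at 128 by about 8 percentage points. At about 0.37, it belongs to 128 and overstates power at 104 by about 9 points. The article does not show which holds, nor that any power has been lost. The sentence still has to be corrected, because the planned size is a figure against which the trial will be judged.

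**What to change.** Correct the sentence in the Participants section so that it:

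1. gives a total and a per-group number that agree;
2. says which number is to be randomised and which is needed for analysis, if they differ;
3. states the baseline to Day-90 correlation used in the power calculation;
4. states the attrition allowance actually planned, if there is one, taken from the planning records and not back-calculated from 128 and 104;
5. if the power claim refers to 128, restates the power or the detectable effect to match the correlation used (about 88% at f = 0.14, or f of about 0.125 at 80%, if that correlation was 0.5).

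The cost is one or two sentences of protocol text. No recruitment change is needed if 128 is already the working target. If the working target is 104, moving to 128 would mean 24 more participants, and that is a decision for the sponsor which the correction of wording does not by itself require.

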### Procedure

Testing will be conducted at the Centre for Human Psychopharmacology (CHP), Swinburne University of Technology, Melbourne, VIC, Australia over a 12-month period. Initial telephone screening will be conducted over the phone, and participants determined eligible for inclusion in the study will be booked in for a Screening visit (Day-7). At the screening visit, participants will attend CHP where informed consent will be obtained and their final eligibility will be confirmed by an experienced research assistant. Demographic information will be collected (age, height, weight, education, gender, handedness, English language skills and employment status) and participants will be screened for dementia using the Memory Assessment Clinic-Q (MAC-Q; Folstein et al., 1975) whereby a score ≥19 will be required for inclusion in the study. Participants will then complete a practice session including all CogTrack tasks and other cognitive assessments.

Prospective and retrospective memory questionnaire (PRMQ)	X		X	X	X
Profile of Mood States (POMS)	X		X	X	X
Wechsler memory scales (WMS-IV)	X	X			X
Neuropsychological battery (*DSST, WAIS-III Digit Span, TMT-A/B, IT, RAVLT*)	X	X			X
Dietary Assessment tool (ASA24)	X	X			X
Cardiovascular Function (*Brachial blood pressure, SphygmoCor measures*)	X				X
Biochemical assessment (fasting blood sample for F2-isoprostanes, liver enzymes, CoQ_10_, C reactive protein)	X				X
Safety (adverse event reporting)	X		X	X	X
Treatment compliance log	X		X	X	X
6 minute walk		X			X
BPro Wrist watch		X			X

### Primary Outcome

The primary study outcome is the effect of CoQ_10_ (Ubiquinol) supplementation on cognitive performance at 90-days, using the composite measures from the CogTrack battery (Wesnes et al., 2017a,b, 2018; Watson et al., 2018). CogTrack is a well-validated and highly sensitive online computerized battery for assessing cognitive function across domains of attention, concentration and vigilance, working memory and executive control, and episodic/declarative memory. Scores from the individual CogTrack tests are used to calculate five index scores: attentional intensity index, sustained attention index, working memory capacity index, episodic memory capacity index, and speed of retrieval index.

### Secondary Outcomes

The secondary outcomes include effects of CoQ_10_ supplementation on a range of cognitive, mood, cardiovascular function and endurance, and biochemical outcomes: (i) 30- and 60-day CogTrack composite scores; (ii) other cognitive measures at 90-days including the Wechsler memory scales, revised (WMS-IV; Wechsler, 1997), Digit symbol substitution test (DSST) and Digit Span test from the Wechsler Adult Intelligence Scale III (WAIS-III; Wechsler, 1997), Trail Making Tests (A and B), Inspection time (IT), and Rey’s Auditory Verbal Learning Test (RAVLT; Rey, 1964); (iii) 30-, 60- and 90-day Profile of Mood States Questionnaire (POMS; McNair et al., 1971) score; (iv) 30-, 60- and 90- day PRMQ (Crawford et al., 2003) score; (v) 90-day Cardiovascular function (brachial blood pressures and aortic blood pressures and reflection calculated using Sphygmocor); (vi) 90-day 6 MWT, (vii) 90-day Oxidative Stress biomarkers [F2-isoprostanes, Glutathione peroxidase (GPX), High-sensitivity C-Reactive Protein]; and (vii) 90-day Liver Function assessments (total bilirubin, total protein, albumin, globulin, alkaline phosphatase, alanine aminotransferase, gamma glutamyl transferase).

In addition, participants will be required to complete online diet recall assessments on six occasions in their own home. This data will be used to understand whether diet plays a role in any of the outcome measures. The cardiovascular measures provide mechanistic variables in which may assist us in better understanding any cognitive benefits of the treatments and the liver enzymes will assist us in monitoring participant safety.

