## Abstract

**Introduction**: With an aging population there is an important need for the development of effective treatments for the amelioration of cognitive decline. Multiple mechanisms underlie age-related cognitive decline including cerebrovascular disease, oxidative stress, reduced antioxidant capacity and mitochondrial dysfunction. CoQ_10_ is a novel treatment which has the potential to improve brain function in healthy elderly populations due to established beneficial effects on mitochondrial function, vascular function and oxidative stress.

**Methods and Analysis**: We describe the protocol for a 90-day randomized controlled trial which examines the efficacy of Ubiquinol (200 mg/day) vs. placebo for the amelioration of cognitive decline in a healthy (non-demented) elderly sample, aged 60 years and over. The primary outcome is the effect of Ubiquinol at 90 days compared to baseline on CogTrack composite measures of cognition. Additional cognitive measures, as well as measures of cardiovascular function, oxidative stress, liver function and mood will also be monitored across 30-, 60- and 90- day time points. Data analyses will involve repeated measures analysis of variance (ANOVA).

**Discussion**: This study will be the first of its kind to provide important clinical and mechanistic data regarding the efficacy of Ubiquinol as a treatment for age-related cognitive decline in the healthy elderly with important implications for productivity and quality of life within this age group.

**Clinical Trial Registration**: The trial has been registered with the Australian and New Zealand Clinical Trials Registry (ANZCTRN12618001841268).

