## A Randomized-Controlled Trial of Ubiquinol in the Healthy Elderly

### Aims and Hypotheses

The primary aim of the current study is to examine the chronic effect of 90-day supplementation with CoQ_10_ (Ubiquinol) on cognitive function in a healthy (non-demented) elderly population. The rationale for focussing on older participants is that this population is more sensitive to cognitive improvement given that increasing age is typically associated with cognitive decline-particularly memory and there is currently a scarcity of previous research using sensitive domain-specific measures investigating the cognitive effects of CoQ_10_ in elderly participants without dementia. Further, levels of CoQ_10_ decrease with age, there is increased deterioration in the cardiovascular system with age and finally, there is increased oxidative stress with age and less anti-oxidant protection. All of these indicators suggest that supplementation with CoQ_10_ could improve cognitive function in the healthy elderly. It is hypothesized that 90-day supplementation with Ubiquinol will result in improved cognitive function in healthy elderly participants aged 60 years or older, using a battery of well-validated highly sensitive measures. The potentially positive effects of CoQ_10_ on cardiovascular measures, oxidative stress biomarkers, liver function and mood will also be examined in secondary exploratory analyses.

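### Liver results are presented as safety monitoring, in the Abstract at Days 30, 60 and 90, but the schedule gives them only before treatment and at Day 90, and the one analysis named compares arm means

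*Protocol article*

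**What the plan says.** **Role.** Aims and Hypotheses groups the liver with outcomes on which the supplement might do good: "liver function and mood will also be examined in secondary exploratory analyses". Secondary Outcomes lists a seven-analyte panel, "90-day Liver Function assessments (total bilirubin, total protein, albumin, globulin, alkaline phosphatase, alanine aminotransferase, gamma glutamyl transferase"), and closes by adding that "the liver enzymes will assist us in monitoring participant safety".

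**Timing.** The Abstract states that "liver function and mood will also be monitored across 30-, 60- and 90- day time points". Secondary Outcomes gives Day 90 only. In Table 1 the row "Biochemical assessment (fasting blood sample for F2-isoprostanes, liver enzymes, CoQ_10_, C reactive protein") is marked once before treatment and once at Day 90, with nothing at Day 30 or Day 60. Procedure describes a fasting blood sample at the baseline visit, repeats that visit's procedure at Day 90, and has participants do the Day 30 and Day 60 assessments online from home.

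**Analysis.** Statistical Analysis says "Similar statistical techniques will be used to investigate the effects of treatment on secondary outcomes". The technique referred to is the primary repeated-measures ANOVA, with treatment between groups and "study visit as a repeated within-group factor (baseline, 90-days"). Results are to be given as effect sizes with 95% confidence intervals. No separate summary of the liver results is named.

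**The concern.** There are two linked problems.

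First, monitoring implies that results become available while participants are taking the capsules. On the Table 1 schedule the only post-baseline liver result comes when the 90-day course is complete. It can describe safety at the end of treatment, but it cannot monitor anyone during it. The Abstract goes further and tells the reader that liver function is followed at Days 30 and 60, for which no blood sample is described.

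Second, liver harm from a supplement would more plausibly appear as marked rises in a few people than as a shift of the whole arm. A comparison of arm means responds to the second pattern and largely misses the first, partly because the extreme values also inflate the variance. At stake is a reassuring sentence in the results paper, such as no effect of treatment on liver function, resting on an analysis with little ability to show the kind of harm the panel is said to watch for.

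**Working it through.** **1. The timing statements side by side**

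| Place | Liver results at |
|---|---|
| Abstract | Days 30, 60 and 90 |
| Secondary Outcomes | Day 90 |
| Table 1, biochemical row | one pre-treatment visit and Day 90 |
| Procedure | blood at baseline, same procedure at Day 90; Days 30 and 60 online from home |

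The column marks in Table 1 may be displaced in the text available (screening appears under Day 0, randomization under Day −7). I therefore read the first biochemical mark as the pre-treatment baseline sample described in Procedure. On any reading there is no mark at Day 30 or Day 60. Three places agree with one another and the Abstract does not.

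**2. What the named analysis tests**

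With two groups and two visits, the visit × treatment interaction equals a two-sample t test on change from baseline to Day 90. The article gives no figure for any liver analyte, so there is nothing of the plan's own to reproduce, and every ALT input below is assumed. Participants section: 128 in total (64 per arm if split equally), printed beside 52 per group. Both are shown; that mismatch is a separate matter.

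**3. Worked case**

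Assume an SD of change of 8 U/L, a rise of 100 U/L in r = 3 of n = 64 Ubiquinol participants, and none on placebo.

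- Mean difference: 100 × 3/64 = 4.69
- Variance of change, Ubiquinol arm: 8² + 100² × (3/64) × (61/64) × (64/63) = 64 + 453.9 = 517.9
- Standard error: √[(517.9 + 64)/64] = 3.02
- Expected t ≈ 4.69/3.02 = 1.55, against a critical value of 1.98 on 126 df

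The remaining scatter in t is 8 × √(2/64)/3.02 = 0.47, so the chance of exceeding 1.98 is about P(Z > (1.98 − 1.55)/0.47) ≈ 0.18. Simulation of the same case gives 0.187.

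**4. Range over assumptions**

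Simulated proportion of trials with p < 0.05. Set A: ALT mean 22, SD 8, visit correlation 0.7, affected participants at 150 at Day 90. Set B: SD of change 8, rises of 60 to 100.

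| Affected on Ubiquinol (placebo 0) | A, n = 64 | A, n = 52 | B, n = 64 | B, n = 52 |
|---|---|---|---|---|
| 2 | 4.0% | 2.9% | 8–9% | 7–9% |
| 3 | 16.2% | 16.1% | 16–19% | 17–19% |
| 4 | 48.7% | 52.1% | 29–39% | 31–42% |

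With three affected, the comparison is therefore non-significant in about 81 to 84% of trials.

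**5. Why larger rises do not help**

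If the rises dwarf ordinary variation and are equal in size, the rise cancels from numerator and denominator and t tends to √[r(n − 1)/(n − r)]. For n = 64 this is √(2 × 63/62) = 1.43 for r = 2, √(3 × 63/61) = 1.76 for r = 3 and √(4 × 63/60) = 2.05 for r = 4. Up to three affected, the limit stays below 1.98 however severe the rises. This step needs no ALT value.

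**6. Would a formal test of counts do better?**

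No. Fisher's exact two-sided p for 3 vs 0 of 64 per arm is 2 × (64 × 63 × 62)/(128 × 127 × 126) = 0.24; for 4 vs 0 it is 0.12. The gain from counts lies in showing the individuals, not in power.

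**The case against.** The strongest reply is that this is a condensed article. Abnormality limits and safety tables commonly sit in a full protocol or analysis plan, and their absence here is no fault. Nor does the article say that individual liver results go unreviewed. That stands. A reader might infer that the liver panel is analysed only by ANOVA and so cannot serve safety at all, but the documents do not support this. Adverse events are collected at Days 30, 60 and 90 (Table 1), and the Discussion promises to report them.

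A reader might also infer that the two roles are incompatible. They are not: a laboratory panel can be both an exploratory outcome and a safety check, and the wording that the enzymes will assist suggests a supplement to other safety data. The Discussion's remark on weighing cost against benefit follows from its sentence on adverse effects, so it should not be read as resting on the liver ANOVA. The ANOVA is also not a comparison of Day 90 means alone, since it models baseline and Day 90. And because effect sizes with intervals are planned, a bare statement of non-significance is not the stated form of reporting.

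Finally, the simulated percentages rest on assumed inputs, and a significance test on counts would not reject for 3 vs 0 or 4 vs 0. So the figures cannot show that a formal test of counts is superior.

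None of this touches the conflict in timing, or the fact that the one analysis the article does assign to the panel is a comparison of means.

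**Conclusion.** The concern holds in limited form. The Abstract's liver monitoring at Days 30, 60 and 90 conflicts with Table 1, Procedure and Secondary Outcomes, and on the latter schedule the claim to monitor safety is not met during treatment. This part rests on the text alone. The comparison of means is poorly suited to the stated safety purpose: two to three marked rises would usually leave it non-significant (rejection about 3 to 9% with two, 16 to 19% with three). Those percentages are illustrative and depend on assumed ALT values. The limiting argument, that up to three very large equal rises among 64 cannot carry t past its critical value, does not depend on them. The comparison can still detect a general shift in the arm, so it remains reasonable for the exploratory role. The point should be corrected, but it does not threaten the primary conclusion.

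**What to change.** 1. Reconcile the Abstract with Table 1, Procedure and Secondary Outcomes on when liver results are obtained. If the Table 1 schedule stands, remove liver function from the Abstract's Day 30 and Day 60 statement and describe it in Secondary Outcomes as an end-of-treatment safety assessment instead of monitoring.
2. State in Aims and Hypotheses and in Secondary Outcomes that the panel is an exploratory outcome, a safety outcome, or both. It need not be dropped from the exploratory list.
3. In Statistical Analysis, add for the safety role: for each analyte, the number and percentage in each arm outside the laboratory reference range at Day 90, and a baseline-to-Day-90 shift table (normal/abnormal). Present these descriptively.
4. State that a non-significant ANOVA will not be interpreted as evidence of liver safety.

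Cost: some rewording and one extra table; the wording and table changes need no new samples or visits. The counts will be imprecise with 52 to 64 participants per arm and should be presented as such.
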